### Outcome Measures

#### Primary Outcome

The primary outcome of this study is the difference in patients’ KAP on VTE at 3-month follow-up between the mVTEA management group and the routine management group.

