#### Statistical Analyses

In this study, we define 2 analysis populations: full analysis set (FAS) and intention-to-treat (ITT). FAS is the set of all patients who have received VTE prevention and treatment intervention at least once after randomization. The ITT set will include all randomly assigned patients, regardless of whether they completed the study or followed the study protocol. FAS will be the primary analysis population, and ITT will provide supportive results. Missing data will be handled using the multiple imputation method. Since the study outcomes already include assessments of safety data, the safety analysis set is not performed. Sensitivity analysis will be conducted by comparing the results of the ITT and FAS analyses.

Continuous variables will be presented as mean and SD, or as median and IQR for variables not following a normal distribution. Categorical variables will be presented as counts and percentages. Differences in baseline demographic and clinical characteristics, as well as survey data between groups, will be assessed using the Student *t* test or the Mann-Whitney *U* test for continuous variables, depending on distributional assumptions. Categorical variables will be analyzed using the chi-square test or Fisher exact test, as applicable.

To account for the repeated measurements of EQ-5D-5L and KAP survey data collected at discharge and the 3-month follow-up, we will use a linear mixed-effects model for repeated measures. The model will include fixed effects for the treatment group (mVTEA management vs routine management), time point (discharge vs 3-month follow-up), the interaction between treatment group and time point, the baseline score of the respective survey (EQ-5D-5L or KAP), and the prestratification factors (VTE diagnosis status at discharge: Yes or No; age: ≥60 years vs <60 years). Patients and their hospitalization units will be included as random effects. The key parameter of interest for evaluating the intervention effect over time will be the group-by-time interaction term. The Cox proportional hazards model will be used to compare the hazard of the event (time to event) between groups during the follow-up period, taking into account the prestratification factors. The hazard ratio and its corresponding 95% CI will be calculated using this model. Statistical significance is set at *P*<.05 (2-sided). SPSS (version 22.0; IBM Corp) will be used for statistical analysis.

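### The primary mixed model uses the discharge KAP score as both response and covariate; the covariate drops out of the key contrast and, with a patient random intercept, the standard error is too small

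*Protocol article*

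**What the plan says.** The Primary Outcome section reads: "The primary outcome of this study is the difference in patients’ KAP on VTE at 3-month follow-up", compared between the two arms. Statistical Analyses introduces a linear mixed-effects model with the words "To account for the repeated measurements of EQ-5D-5L and KAP survey data collected at discharge and the 3-month follow-up". Its fixed effects are group, "time point (discharge vs 3-month follow-up"), and then "the interaction between treatment group and time point, the baseline score of the respective survey (EQ-5D-5L or KAP), and the prestratification factors" (age group and VTE diagnosis). On the random part it says: "Patients and their hospitalization units will be included as random effects". On the test: "The key parameter of interest for evaluating the intervention effect over time will be the group-by-time interaction term".

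Table 3 schedules the VTE-KAP questionnaire and the EQ-5D-5L only at enrollment (discharge) and at month 3. The baseline score in the model can therefore only be the discharge score that is already a response.

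**The concern.** On every discharge row the response equals one of the covariates. Two consequences need checking.

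- Does the covariate do anything for the parameter that is tested?
- Is the standard error of that parameter right, given that half the rows have an artificially small residual?

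This model supplies the p-value and confidence interval for the primary outcome, and the same wording governs EQ-5D-5L. If the standard error is too small, the trial declares an effect too often. That matters more here because participants are not blinded and the questionnaire is self-administered.

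**Working it through.** **Inputs from the protocol.** Coefficient of variation 0.1, difference 5%, 100 per group, two-sided alpha 0.05 (Sample Size and Power Considerations); model terms as above; missing data multiply imputed, so each analysed data set has both visits for every patient.

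**Assumptions, not in the protocol.** ρ, the correlation between discharge and 3-month KAP; k, the 3-month SD divided by the discharge SD. Both are varied below.

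**1. The plan's own power.** Standardised difference 5/10 = 0.5; SE = √(2/100) = 0.1414; ratio 3.536. Power is Φ(3.536 − 1.960) = 94.2% at alpha 0.05 and Φ(3.536 − 2.241) = 90.2% at 0.025. The stated 94% and 90% reproduce, as a plain two-sample comparison of scores without baseline adjustment.

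**2. The interaction estimate.** Write y0 for the discharge score and y1 for the 3-month score. With two visits the interaction is a between-arm contrast of y1 − y0. The baseline score and the stratification factors take the same value on both rows of a patient and cancel. The estimate is the unadjusted difference in mean change. In simulation the two agreed to rounding error (largest gap 7e-16).

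**3. The residuals.** Scale the discharge SD to 1. The true slope on y0 is 1 on the discharge rows and ρk on the 3-month rows. The model allows one slope, b = (1 + ρk)/2. Then:

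- discharge residual variance: (1 − ρk)²/4
- 3-month residual variance: (1 − ρk)²/4 + k²(1 − ρ²)
- within-patient residual covariance: −(1 − ρk)²/4

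The covariance is never positive. A random intercept can represent only a non-negative covariance, so its variance is estimated as zero. In 1,000 REML fits at each of ρ = 0.3, 0.5, 0.7 and 0.9 (k = 1) it was zero every time.

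**4. The standard error.** With patient variance zero, the model takes the variance of a change as twice the average residual variance: (1 − ρk)²/2 + k²(1 − ρ²). The true variance is 1 + k² − 2ρk = (1 − ρk)² + k²(1 − ρ²). Hence

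model/true variance = 1 − (1 − ρk)² / [2(1 + k² − 2ρk)],

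which is (3 + ρ)/4 when k = 1. It never exceeds 1 and equals 1 only when ρk = 1.

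**5. Actual error of a nominal 5% test**, 2[1 − Φ(1.96 × √ratio)]:

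| ρ | k | variance ratio | SE ratio | actual error |
|---|---|---|---|---|
| 0.3 | 1 | 0.825 | 0.908 | 7.5% |
| 0.5 | 1 | 0.875 | 0.935 | 6.7% |
| 0.7 | 1 | 0.925 | 0.962 | 5.9% |
| 0.9 | 1 | 0.975 | 0.987 | 5.3% |
| 0.5 | 0.8 | 1 − 0.36/1.68 = 0.786 | 0.886 | 8.2% |
| 0.5 | 1.2 | 1 − 0.16/2.48 = 0.935 | 0.967 | 5.8% |

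Simulation at 100 per arm with k = 1 gave 7.4%, 6.4%, 5.9% and 5.3% for the first four rows. Analysis of covariance (ANCOVA) on the 3-month score gave 4.6% to 5.0% across the simulated null settings. The hospitalization-unit effect was not fitted in these runs. A unit intercept is also constant within a patient and should not change the interaction estimate.

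**6. Power of valid tests** (100 per group, k = 1, SD 10, difference 5). SD for change: 10√[2(1 − ρ)]; for ANCOVA: 10√(1 − ρ²).

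| ρ | change score | ANCOVA |
|---|---|---|
| 0.3 | SD 11.83, power 84.8% | SD 9.54, power 96.0% |
| 0.5 | SD 10.00, power 94.2% | SD 8.66, power 98.3% |

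**The case against.** The best defence has four parts.

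- **The estimate is sound.** A reader might infer that the test ignores the discharge score. It does not: that score enters by subtraction. Nor does testing change contradict a primary outcome defined at 3 months, since under randomization both contrasts have the same expectation. This stands; the trouble is with the error bars and efficiency, not bias.
- **The standard error depends on the covariance structure.** A structure that allows negative within-patient correlation, such as compound symmetry, gives the ordinary change-score standard error; a simulation at ρ = 0.5 then gave 4.9% to 5.1% error. The article refers to a statistical analysis plan that is not shown, and a residual structure could be set there. This makes the claim conditional but does not remove it: the text names a patient random effect and no other structure. A reader might also argue that an unstructured covariance would make the fit degenerate, but the protocol does not name that structure.
- **The inflation may be small.** True when ρk is near 1. It is never in the conservative direction.
- **Being less efficient than ANCOVA is not an error.** Fair: a valid change-score test reaches the planned 94% once ρ is about 0.5 or more. A shortfall arises only at lower correlation.

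A reader might also see the t and Mann-Whitney tests of survey data as a rival primary analysis. They sit with the descriptive and baseline comparisons, and the next paragraph names the interaction as the key parameter, so the text does not support that.

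**Conclusion.** The model is wrong as written. The double use of the discharge score is explicit and the schedule leaves no other reading. With both visits present for every patient, the covariate certainly does nothing for the interaction.

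That the standard error is too small holds for a patient random intercept with variance at or above zero and a common residual variance. On that reading, the nominal 5% error becomes about 6% to 7.5% for ρ from 0.7 down to 0.3 at equal SDs. At ρ = 0.5 it is about 8.2% if the 3-month SD is 0.8 of the discharge SD, and 5.8% if it is 1.2 times that SD. It becomes negligible as ρk approaches 1. These sizes rest on assumed values of ρ and k; the direction does not. The documents do not support going further and calling the treatment estimate biased or the standard error wrong under every covariance structure.

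**What to change.** Replace the model description for the primary analysis. Use the 3-month total KAP score as the only response, with group, discharge KAP, age stratum and VTE-status stratum as fixed effects and hospitalization unit as a random effect. Report the adjusted 3-month difference with its 95% CI. This restores the 5% level and gives about 96% and 98% power at ρ = 0.3 and 0.5 with 100 per group.

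An equally acceptable alternative keeps both visits as responses, removes the baseline covariate and constrains the arms to a common discharge mean.

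Use the same model for EQ-5D-5L. The cost is a change of wording made before unblinding; no new data are needed.

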### Ethical Considerations

This study will be conducted by the principles outlined in the Declaration of Helsinki, ensuring that no additional harm or risks are imposed upon the participants. The ethics committee of the Sixth Medical Center of the Chinese People’s Liberation Army General Hospital has already provided ethics approval (HZKY-PJ-2024-8). Before the commencement of the clinical trial, all participants will receive comprehensive information about the trial’s purpose, the procedures to be undertaken, the anticipated duration, and the potential risks and benefits. They will then voluntarily provide written informed consent. To maintain participant confidentiality, real names will not be used in case reports, and participants will retain the right to withdraw from any aspect of the study at any time. Research findings will be disseminated through publication in peer-reviewed journals and presentations at provincial, national, and international conferences or forums.

## Results

Figure 4 describes the study flowchart. Participants are currently being recruited. The first participant was enrolled in August 2024, marking the official start of the study. The recruitment process is expected to be completed in June 2025. As of the submission of the paper, 185 patients were enrolled in this clinical trial. All included patients were followed up according to the outlined schedule.

**Figure 4 figure4:**
[figure not shown]
Flowchart of the trial. C-eHEALS: Chinese version of electronic health literacy scale; HBM: health belief model; KAP: knowledge, attitude, and practice; mHealth: mobile health; mVTEA: smart technique-assisted patient-centered care mHealth app for managing venous thromboembolism; VTE: venous thromboembolism.

## Discussion

### Expected Outcomes

The SmaVTE study is an innovative study designed to address the multifaceted challenges of VTE management through the integration of smart technology. This trial aims to evaluate the effectiveness of the mVTEA app in VTE management, which is an mHealth app designed to enhance patient-centered care through the joint use of HBM and KAP theoretical frameworks. This study hypothesizes that such theory-based mHealth interventions can improve the KAP level for patients with or at risk of VTE while ensuring their safety compared to traditional face-to-face VTE management.

Unlike previous mHealth studies that focused mainly on patients with warfarin therapy, targeting patients with AFI and heart valve disease [26,64-66], the SmaVTE study expands the target population to include both patients at risk for VTE and those already diagnosed, as well as patients using direct oral anticoagulants (DOACs). This comprehensive scope is designed to reflect real-world clinical practice and address emerging challenges associated with DOAC management, such as renal impairment, drug interactions, and the absence of specific reversal agents [45,67]. Integrating the ABCDEF pathway into the KAP framework further supports a comprehensive and dynamic approach to VTE care, encompassing not only anticoagulation management but modifiable risk factors, long-term complications, and comorbidities. If proven effective, findings from this trial may have significant implications for clinical practice, supporting more proactive and personalized approaches to VTE prevention and treatment.

The theoretical foundation of the mVTEA app is grounded in the principles of patient-centered care and behavioral science theories. Patient-centered care emphasizes tailoring medical care to individual patient needs, preferences, and values [15,16]. Behavioral science theories, such as the HBM and the KAP theories, suggest that empowering patients with information and involving them in their care can significantly enhance motivation and adherence to treatment protocols [31-34]. The mechanisms by which the mVTEA app may influence behavior change can be attributed to several factors, including goal setting, real-time feedback, personalized reminders, and tailored health education programs. These features are designed to facilitate continuous engagement and allow patients to monitor their progress, thereby enhancing motivation and adherence.

### Limitations

There were some limitations to this study. First, the applicability of the results may be confined to the population studied and may not fully extrapolate to other patient groups, such as those with AFI or heart valve disease. Second, the study encompasses only those patients who can use smartphones or computer tablets, which introduces a potential bias related to the participants’ digital literacy. To mitigate this effect, standardized training on the application’s use will be provided following the patient’s registration on the mVTEA app. Third, the experimental protocol could not implement double blinding, a limitation inherent to the specificity of mHealth interventions. To ensure the reliability of the data, blind statistical analysis will be conducted, and roles among interventionists, efficacy evaluators, and statisticians will be distinctly segregated. Finally, the clinical outcomes, designated as secondary endpoints in this study, require validation through subsequent research.

### Conclusion

The SmaVTE study may contribute to advances in VTE prevention and treatment. By integrating smart technology with patient-centered care and applying well-established theoretical frameworks, the study aims to enhance the KAP of patients at risk for or diagnosed with VTE while improving clinical outcomes. In addition, this study provides a novel approach for the long-term management of VTE. The results from this trial could have significant implications for clinical practice and may encourage further research into the integration of smart technologies with theory-based behavior change techniques.

## Appendix

Multimedia Appendix 1 Additional material.

## Abbreviations

AFI: atrial fibrillation
AFL: atrial flutter
C-eHEALS: Chinese version of the electronic health literacy scale
DOAC: direct oral anticoagulant
FAS: full analysis set
HBM: health belief model
ISTH: International Society on Thrombosis and Hemostasis
ITT: intention-to-treat
KAP: knowledge, attitudes, and practices
mHealth: mobile health
mVTEA: smart technique–assisted patient-centered care mHealth app for managing venous thromboembolism
PE: pulmonary embolism
QoL: quality of life
SmaVTE: smart technology facilitated patient-centered venous thromboembolism management
SPIRIT: Standard Protocol Items: Recommendations for Interventional Trials
VTE: venous thromboembolism
